**5.2.4. Hospitalization at ED visit**

The counts and proportions of participants admitted to hospital from ED visit in each randomization arm will be reported. To analyze the outcome, we will calculate 95 % confidence intervals (CI) of the differences using a Standard Normal Deviate (SND) test for the proportions. Risk ratios (RR) with 95 % CI are calculated.

**5.2.5. Hospitalization within 7 days after study entry**

This outcome is defined as pediatric patients admitted to hospital within a week (7 days) of the emergency room visit. The counts and proportions of participants admitted to hospital during following 7 days after study entry in each randomization arm will be reported. To analyze the outcome, we will calculate 95 % confidence intervals (CI) of the differences using a Standard Normal Deviate (SND) test for the proportions. Risk ratios (RR) with 95 % CI are calculated.

**5.2.6. Diagnostic tests performed in the emergency room**

The average sum of laboratory diagnostic test with 95 % confidence interval will be calculated for each randomization arm. Chest radiographs will be reported as proportion of participants with chest X-ray performed following 7 days after randomization. To analyze the outcome, we will calculate 95 % confidence intervals (CI) of the differences using a Standard Normal Deviate (SND) test for the proportions. Risk ratios (RR) with 95 % CI are calculated.

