**Subjects are recruited for the trial by a pediatric emergency room nurse upon emergency room registration.** The emergency room nurses have previous experience of recruiting patients from two clinical trials. The subjects recruited to the study can also discuss the trial with the on-call physician. The subjects are asked to provide a written consent, after which they are randomized into groups in a 2:1 ratio (treatment under study:current treatment). The interventions are randomized by trial numbers and enclosed in non-transparent envelopes. After asking for consent, the nurse opens the envelope assigned to the number that tells which group the subject is assigned to. Patients randomized to the new treatment practice are asked to give a sample which is analyzed with the POC device in the emergency room. If there are technical problems with the analysis, the nurse may take a new sample if necessary; a note on the technical problem is entered in the device log. During the trial, the number of technical problems with analysis increased, and the device manufacturer was informed of all tests that had failed. During the trial, over a short period from Sep 8 to 28, 2019, an increase in the number of failed samples was observed (9 out of 56, i.e. 16% of all samples analyzed). According to the manufacturer, this was to a significant degree (4 out of 9, 45%) associated with problems with the sample cassette transportation chain and wrong storage temperature during transportation. As technical problems persisted, the operating system of the POC test device was updated on Jan 7, 2020.

If an unforeseen adverse event occurs during sampling, an adverse event report is recorded in the hospital's internal adverse event reporting system; in addition, the investigators are informed of the event. The POC test results are automatically recorded in Weblab and are thus available at the doctor's appointment. Samples are only taken at the on-call physician's discretion from the children randomized to the current treatment group. The samples are stored in the emergency room and transported to the laboratory for analysis at 7 am the next morning. The results are entered into Weblab in the microbiology lab, and the on-call physician is responsible for reporting the results and reacting to them.

Due to the SARS-CoV2 epidemic and change in testing practices, randomization was halted on March 13, 2020 at 3 pm when 1,350 subjects had been recruited.

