### 2.6.2. Secondary outcome measures

|          | Outcome                                                                                                                     | Definition of outcome in ClinicalTrials                                           |
|----------|-----------------------------------------------------------------------------------------------------------------------------|-----------------------------------------------------------------------------------|
| 1 | Treatment with antibiotics initiated within a week (7 days) of the emergency room visit and different groups of antibiotics | Proportion of children with antibiotics in one week                               |
| 2 | Macrolide antibiotics prescribed in the ED                                                                                  | Proportion of children receiving macrolide antibiotic at pediatric emergency room |
| 3 | Macrolide antibiotics started in infants                                                                                    | Proportion of infants aged < 3 months receiving                                   |

|    |                                                                                        |                                                                                                                               |
|----|----------------------------------------------------------------------------------------|-------------------------------------------------------------------------------------------------------------------------------|
|    | under 3 months (proportion)                                                            | macrolide antibiotic at pediatric emergency room                                                                              |
| 4  | Immediate admittance to hospital from emergency room (hospitalized pediatric patients) | Proportion of children admitted to hospital                                                                                   |
| 5  | Hospital admissions within a week after emergency room visit                           | Proportion of children admitted to hospital within one week after study entry                                                 |
| 6  | Other diagnostic tests performed in the emergency room                                 | Number of other diagnostic tests than point-of-care test performed at emergency room                                          |

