| 7  | Revisits to emergency room within the next 7 days                                      | Proportion of children admitted to hospital or revisit at emergency room within 7 days after study entry                      |
| 8  | Outpatient phone contacts and their number (with nurse or physician) within 7 days     | Proportion of children with outpatient telephone contact within 7 days after discharge from emergency room                    |
| 9  | Ancillary laboratory testing                                                           | Number of diagnostic tests per child other than point-of-care test performed within one week                                  |
| 10 | Intensive care                                                                         | Proportion of children with admission to pediatric intensive care unit or intensive care unit within 7 days after study entry |
| 11 | Mortality within the next 30 days after the emergency room visit                       | Proportion of children who died within one month after study entry                                                            |
| 12 | Visit associated costs                                                                 | Cost in euros per child per visits                                                                                            |
| 13 | Length of stay at ED                                                                   | Length of stay at emergency room in minutes                                                                                   |
| 14 | Pathogen directed therapy                                                              | Proportion of children receiving correct pathogen directed therapy                                                            |
| 15 | Time from emergency room visit to onset of pathogen-directed treatment                 | Time to initiation of correct pathogen directed therapy                                                                       |

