#### **5.2.9. Ancillary laboratory testing**

This outcome is defined as the mean count of laboratory tests performed on each participant and proportion of participants with chest X-ray at ED or any radiological imaging within 7 days after study entry. The average sum of laboratory tests will be calculated and reported for each randomization arm. To analyze the outcome, a t-test for continuous valuables with 95 % confidence interval will be calculated. The counts and proportions of participants with chest X-ray at ED of any radiological imaging will be reported. To analyze the outcome, we will calculate 95 % confidence intervals (CI) of the differences using a Standard Normal Deviate (SND) test for the proportions. Risk ratios (RR) with 95 % CI are calculated.

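### SAP 5.2.6 analyses an emergency-room testing outcome with a 7-day chest X-ray measure, and SAP 5.2.9 leaves unclear which imaging measure belongs to the one-week outcome

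*Combined protocol and SAP*

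**What the plan says.** Two secondary outcomes deal with testing, and SAP 2.6.2 separates them by time window. Row 6 is the visit outcome: "Number of other diagnostic tests than point-of-care test performed at emergency room". Row 9 is the one-week outcome: "Number of diagnostic tests per child other than point-of-care test performed within one week". Protocol 4.6 also lists tests in the emergency room and ancillary laboratory testing as separate items, but gives no window for the second and mentions chest X-ray in neither.

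The analysis of row 6 is in SAP 5.2.6, headed "Diagnostic tests performed in the emergency room". For laboratory tests it says "The average sum of laboratory diagnostic test with 95 % confidence interval will be calculated for each randomization arm" and states no window. For imaging it says "Chest radiographs will be reported as proportion of participants with chest X-ray performed following 7 days after randomization".

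The analysis of row 9 is in SAP 5.2.9. Its definition sentence combines a mean count of laboratory tests with the "proportion of participants with chest X-ray at ED or any radiological imaging within 7 days after study entry". The later reporting sentence reads: "The counts and proportions of participants with chest X-ray at ED of any radiological imaging will be reported".

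**The concern.** The two outcomes answer different questions. The ED outcome asks whether having the pathogen result during the visit spares work-up at that visit. The one-week outcome asks whether total testing over the episode changes. Protocol section 6 points to both routes when it argues that the test might reduce further testing or in-hospital monitoring.

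A chest X-ray counted over 7 days mixes the two. It includes imaging on the ward and at revisits, and admissions and revisits are themselves trial outcomes (SAP 5.2.4, 5.2.5 and 5.2.7). A reader of a results table headed as ED testing would take the figure as visit-level imaging. The same reader might set it beside the ED X-ray rates in the protocol's literature tables, although the window differs. The SAP exists to settle such choices before the data are examined, and here two analysts could follow it faithfully and report different quantities.

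**Working it through.** No sample size, power or error rate is involved, and the plan states no figure to reproduce. The check is a comparison of texts.

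1. Setting and window at each place.

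| Place | Setting or window |
|---|---|
| Protocol 4.6, diagnostic tests item | emergency room |
| SAP 2.6.2 row 6 | emergency room |
| SAP 5.2.6, heading | emergency room |
| SAP 5.2.6, laboratory sentence | none stated |
| SAP 5.2.6, chest X-ray sentence | 7 days after randomization |
| SAP 2.6.2 row 9 | one week |
| SAP 5.2.9, definition sentence | chest X-ray at ED, *or* any imaging within 7 days |
| SAP 5.2.9, reporting sentence | chest X-ray at ED *of* any imaging; no window |

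2. What the 7 days contain. Protocol 4.5 states: "Subjects are recruited for the trial by a pediatric emergency room nurse upon emergency room registration". Randomization follows consent at that point. The window therefore covers the index visit and everything after it up to day 7, including a ward stay and any revisit. An X-ray on the ward on day 3, or at a revisit on day 6, meets the wording of 5.2.6 without being a test of the index ED visit.

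3. Consequence for the 5.2.6 figure. Let *e* be the proportion with an X-ray during the ED visit and *r* the proportion, among the remaining children, who have their first X-ray later within 7 days. The measure as written is *e* + (1 − *e*) × *r*. This is never smaller than *e*, and it equals *e* only if *r* is zero or *e* is one. The documents give neither *e* nor *r* for this trial, so the gap cannot be calculated.

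4. What 5.2.9 specifies. Its definition can be read as two measures (ED chest X-ray; any imaging within 7 days) or as one composite in which either counts. The reporting sentence changes *or* to *of* and drops the window, so it does not settle the matter. It is also unclear whether the 7 days in the definition apply to the laboratory count.

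5. Whether separation was intended. For hospitalization the SAP keeps the index visit (5.2.4) and 7 days (5.2.5) as distinct outcomes with matching analysis text. Rows 6 and 9 set up the same pair for testing. Only the analysis text of 5.2.6 and 5.2.9 loses it.

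**The case against.** The best reply is that this is a labelling slip with little loss. The sentence in 5.2.6 states its own window, so a careful report would show it. An ED chest X-ray is named in 5.2.9. If the components there are read as separate measures, the two sections together yield ED chest X-ray, 7-day chest X-ray and 7-day imaging of any kind. Nothing would be missing; the measures would merely sit under the wrong headings. This stands in part: the ED comparison is not necessarily lost. It depends, however, on a reading of 5.2.9 that the text does not secure, and 5.2.6 still contradicts its own heading and row 6.

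A reader might infer that the two windows have simply been swapped. The documents do not support that. The 5.2.9 definition goes on to include any imaging within 7 days, so it covers what row 9 requires and is mixed rather than reversed. Nor are the laboratory analyses identical apart from their window: 5.2.9 names a t-test, while 5.2.6 gives only a mean with a confidence interval for each arm.

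A reader might also infer that the window creates a false difference between arms. One can illustrate this with assumed rates: an ED X-ray rate of 20% in both arms, admission of 25–30% with point-of-care testing against 35% in control, and a ward X-ray in 10–30% of admitted children not X-rayed in the ED. The 7-day difference then runs from 0.80 × (0.35 − 0.30) × 0.10 = 0.4 percentage points to 0.80 × (0.35 − 0.25) × 0.30 = 2.4 points. None of these inputs is a rate given for this trial, and the result depends on presuming an admission effect. If admissions did differ, the difference in 7-day imaging would be a real effect of randomization on 7-day imaging, measured alike in both arms. It would be wrongly labelled, not biased.

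**Conclusion.** The inconsistency in SAP 5.2.6 is plain on the page. Followed literally, it gives the ED-testing outcome a chest X-ray measure that is not confined to the ED. SAP 5.2.9 is ambiguous rather than contradictory, and neither section states a clear window for laboratory tests.

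The reach is limited to the imaging and laboratory parts of two of the 15 secondary outcomes. The primary outcome, the sample size and the significance level are untouched. The only quantitative statement the documents allow is one of direction: the 7-day X-ray proportion cannot be lower than the ED proportion. The fault is an ill-defined and mislabelled quantity, and no bias between arms is shown. It merits correction because the remedy is small and the present text leaves the choice of measure to the analyst of an open-label trial.

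**What to change.** In SAP 5.2.6, count chest X-rays and laboratory tests from ED arrival to ED departure only, using the interval already defined for length of stay in SAP 5.2.13. Move the ED chest X-ray from 5.2.9 to this section.

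In SAP 5.2.9, report chest X-ray within 7 days and any radiological imaging within 7 days as two separate measures. This keeps the 7-day chest X-ray as a measure in its own right. State that laboratory tests are counted from study entry to day 7, and repeat the window in the reporting sentence.

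The latest SAP version is dated March 2022, about two years after randomization stopped in March 2020, and it records analyses already done at the request of the review process. The change should therefore be disclosed as a correction made after data collection.

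The cost is a few sentences and a re-tabulation. It requires dates and times of X-rays. SAP 2.10 describes review of hospital medical records but names no imaging source, so their availability is an assumption. If the times cannot be recovered, the fallback is to label the 5.2.6 X-ray measure openly as a 7-day proportion. ED X-ray proportions will be no higher than the 7-day figures, and the report should say why.

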**5.2.7. Readmissions to pediatric emergency room**

This outcome is defined as revisit to any emergency room within next 7 days after study entry. The counts and proportions of participants readmitted to emergency room during following 7 days after study entry in each randomization arm will be reported. To analyze the outcome, we will calculate 95 % confidence

intervals (CI) of the differences using a Standard Normal Deviate (SND) test for the proportions. Risk ratios (RR) with 95 % CI are calculated.

#### **5.2.8. Outpatient telephone contacts**

This outcome will be defined as the proportion of participants with at least one emergency department visit related telephone contact to nurse or physician within following seven days after study entry. The counts and proportions of participants with telephone contact during following 7 days after study entry in each randomization arm will be reported. To analyze the outcome, we will calculate 95 % confidence intervals (CI) of the differences using a Standard Normal Deviate (SND) test for the proportions. Risk ratios (RR) with 95 % CI are calculated.

#### **5.2.9. Ancillary laboratory testing**

This outcome is defined as the mean count of laboratory tests performed on each participant and proportion of participants with chest X-ray at ED or any radiological imaging within 7 days after study entry. The average sum of laboratory tests will be calculated and reported for each randomization arm. To analyze the outcome, a t-test for continuous valuables with 95 % confidence interval will be calculated. The counts and proportions of participants with chest X-ray at ED of any radiological imaging will be reported. To analyze the outcome, we will calculate 95 % confidence intervals (CI) of the differences using a Standard Normal Deviate (SND) test for the proportions. Risk ratios (RR) with 95 % CI are calculated.

#### **5.2.10. Intensive care**

This outcome is defined as proportion of participants admitted to intensive care unit for any reason during following 30 days after study entry. The counts and proportions of participants admitted to intensive care unit during following 30 days after study entry in each randomization arm will be reported. To analyze the outcome, we will calculate 95 % confidence intervals (CI) of the differences using a Standard Normal Deviate (SND) test for the proportions. Risk ratios (RR) with 95 % CI are calculated.

#### **5.2.11. Mortality**

This outcome is defined as proportion of participants who died for any reason during following 30 days after study entry. The counts and proportions of participants to die during following 30 days after study entry in each randomization arm will be reported. To analyze the outcome, we will calculate 95 %

confidence intervals (CI) of the differences using a Standard Normal Deviate (SND) test for the proportions. Risk ratios (RR) with 95 % CI are calculated.

#### **5.2.12. Visit associated costs**

Total costs related to emergency department visit will be collected. The average sum of costs will be calculated and reported for each randomization arm. To analyze the outcome, a t-test for continuous valuables with 95 % confidence interval will be calculated.

#### **5.2.13. Length of stay at ED**

The length of stay at emergency department will be defined as time from arrival at the emergency department to discharge from emergency room or transfer to hospital ward or intensive care unit. The average length of stay at emergency department in minutes will be calculated and reported from each randomization arm. To analyze the outcome, a t-test for continuous valuables with 95 % confidence interval will be calculated.

#### **5.2.14. Proportion of children receiving correct pathogen directed therapy**

This outcome will be defined as proportion of participants with pathogen targeted treatment available in each randomization arm. The counts and proportions of participants in whom the pathogen with targeted treatment available was detected in each randomization arm will be reported. To analyze the outcome, we will calculate 95 % confidence intervals (CI) of the differences using a Standard Normal Deviate (SND) test for the proportions. Risk ratios (RR) with 95 % CI are calculated.

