### 4.2 Trial design

The trial is a single-center, open, parallelly randomized controlled trial comparing immediate point-of-care testing for respiratory tract pathogens to a control group where samples are only taken at doctor's discretion and analyzed in a central laboratory during office hours on weekdays. As we assume that the trial group will benefit from the more rapid diagnostics enabled by the adoption of POC testing, the groups are randomized into two groups in a 2:1 ratio (POC testing : current practice).

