## Secondary outcome measures

- Treatment with antibiotics initiated within a week (7 days) of the emergency room visit and different groups of antibiotics
- Macrolide antibiotics prescribed in the ED
- Macrolide antibiotics started in infants under 3 months (proportion)
- Immediate admittance to hospital from emergency room (hospitalized pediatric patients)
- Pediatric patients admitted to hospital within a week (7 days) of the emergency room visit
- Diagnostic tests performed in the emergency room
- Outpatient phone contacts and their number (with nurse or physician) within 7 days
- Revisits to emergency room within the next 7 days
- Ancillary laboratory testing
- Intensive care or intensive monitoring within the next 30 days after the emergency room visit
- Mortality within the next 30 days after the emergency room visit
- Visit associated costs
- Length of stay at ED
- Pathogen directed therapy (defined as antimicrobial therapy directed against detected pathogen with specific treatment available)
- Time from emergency room visit to onset of pathogen-directed treatment

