### 718 **2.2.2. Secondary objectives**

719 The secondary objectives are to investigate the effect of intervention on antibiotic prescriptions within 7  
720 days after study entry, macrolide antibiotic prescriptions at ED visit, macrolide antibiotics started in infants  
721 under 3 months, hospital admissions during the ED visit and 7 days after study entry, diagnostic tests  
722 performed in the emergency room, outpatient telephone contacts within 7 days after study entry,  
723 intensive care within 30 days after study entry, mortality within the next 30 days after study entry and visit  
724 associated costs.

725

726 Additional outcomes are proportion of children in whom the pathogen with targeted treatment available  
727 (influenza, *Mycoplasma pneumoniae*, *Bordetella pertussis*, *Legionella pneumophila*) was detected,  
728 proportion of participants receiving targeted antimicrobial treatment and time to initiation of targeted  
729 therapy.

730

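### SAP 5.2.14 carries the title of a treatment-received outcome but defines and tests detection of a treatable pathogen, which in expectation favours the arm that is tested routinely

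*Combined protocol and SAP*

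**What the plan says.** Four places describe this outcome.

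- **Protocol 4.6** lists "Pathogen directed therapy (defined as antimicrobial therapy directed against detected pathogen with specific treatment available". The subject is therapy.
- **SAP 2.6.2, row 14** gives the definition entered in the registry: "Proportion of children receiving correct pathogen directed therapy". The same phrase is the heading of SAP 5.2.14.
- **SAP 2.2.2** names two separate additional outcomes, first the "proportion of children in whom the pathogen with targeted treatment available" was detected, then the "proportion of participants receiving targeted antimicrobial treatment". It lists the pathogens as influenza, *M. pneumoniae*, *B. pertussis* and *L. pneumophila*.
- **SAP 5.2.14**, the analysis section, says: "This outcome will be defined as proportion of participants with pathogen targeted treatment available in each randomization arm". It continues: "The counts and proportions of participants in whom the pathogen with targeted treatment available was detected in each randomization arm will be reported". A standard normal deviate test, a 95% CI for the difference and a risk ratio follow.

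On sampling, SAP 2.5.1 has point-of-care children sampled at registration. Protocol 4.2 describes "a control group where samples are only taken at" the doctor's discretion, and protocol 4.5 repeats this.

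**The concern.** Nothing in the body of 5.2.14 requires that a drug was given, or that it was the right one. A child whose influenza or mycoplasma is found and left untreated counts the same as one who is treated. A results line under this heading would be read as treatment received when it is test yield.

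Yield is not a neutral quantity here. One arm is sampled routinely and the other selectively, so the design itself creates a difference in detection. SAP 2.7 sets a null of no difference for every secondary outcome. For detection that null is expected to be false whatever happens to treatment. SAP 5.3 makes no multiplicity adjustment, so a nominally significant result could be reported as a therapy benefit. Meanwhile the question actually posed, whether more children get targeted treatment, would have no comparison of proportions behind it.

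**Working it through.** The documents give no expected rate, effect or power for this outcome, so there is no stated figure to reproduce. The check has two parts.

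**1. The wording side by side**

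| Place | What is counted |
|---|---|
| Protocol 4.6 | Therapy against a detected pathogen |
| SAP 2.6.2 row 14 | Children receiving therapy |
| SAP 2.2.2 | Detection and receipt, as two outcomes |
| SAP 5.2.14 heading | Children receiving therapy |
| SAP 5.2.14 body | Children with a treatable pathogen detected |

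SAP 2.2.2 shows that the plan distinguishes the two quantities. Section 5.2 has one matching comparison of proportions, and it puts the detection count under the receipt title.

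**2. Direction and size**

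Inputs:
- 1,350 recruited (protocol 4.5). At 2:1 this is taken as 900 and 450; the split is assumed.
- True prevalence *p* of a listed pathogen, equal in both arms by randomisation. Not in the documents; 5% and 10% are used as illustrations.
- Share *s* of carriers found by discretionary testing in controls. Not in the documents; range 0.2 to 0.8.
- Point-of-care failure *f*. Protocol 4.5 reports 9/56 = 16% for one three-week period. Taking 16% throughout is a deliberately unfavourable case, since the nurse may resample.

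Expected detection is p(1 − f) with point-of-care testing and p·s in controls, so the expected RR is (1 − f)/s. Prevalence cancels.

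| s | RR, f = 0 | RR, f = 0.16 |
|---|---|---|
| 0.2 | 5.0 | 4.2 |
| 0.4 | 2.5 | 2.1 |
| 0.6 | 1.67 | 1.4 |
| 0.8 | 1.25 | 1.05 |

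With f = 0.16 the RR falls below 1 only when s exceeds 0.84.

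The chance of two-sided P < 0.05 is about Φ[(Δ − 1.96·SE₀)/SE₁], with SE₀ pooled and SE₁ unpooled. For p = 5%, s = 0.4, f = 0:
- Rates are 5.0% and 2.0%, so Δ = 0.03.
- Pooled rate = (45 + 9)/1350 = 0.04.
- SE₀ = √[0.04 × 0.96 × (1/900 + 1/450)] = 0.0113.
- SE₁ = √[0.05 × 0.95/900 + 0.02 × 0.98/450] = 0.0098.
- Φ(0.80) = about 79%.

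The same formula gives about 98% for 10% vs 4%, and about 12% for 5% vs 4%. All of these assume no difference in treatment practice.

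**Effect of correcting the numerator.** For receipt of therapy against a detected pathogen, over all randomised children, expected RR = [(1 − f)/s] × (uptake among detected, point-of-care ÷ control). If uptake is equal, this is the same RR as for detection. The correction makes the endpoint measure treatment; it does not remove the dependence on testing.

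**The case against.** The strongest reply is that this is a drafting slip. The heading of 5.2.14 and the three other places all point to receipt, SAP 1 says the plan follows the latest protocol, and an analyst would probably code receipt. Protocol 4.9 also reports ED antibiotic prescriptions separately as untargeted and pathogen-targeted. This limits the seriousness but does not remove the problem. The operative sentences in 5.2.14 specify detection twice, and the targeted category defined in SAP 2.6.1 excludes antivirals, so it cannot stand in for an outcome that includes influenza.

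A second reply is that detecting more and therefore treating more is the mechanism under test. That is right, and it is why receipt over all randomised children is a legitimate outcome. It does not justify counting detections that led to no treatment.

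Three stronger readings are tempting, and the documents do not support them.
- *A reader might infer that the point-of-care arm is bound to win, and significantly.* Controls can have influenza/RSV results in about 2–3 hours and a laboratory panel covering mycoplasma and pertussis (SAP 2.5.2). Point-of-care samples can be missed or fail (SAP 4.4, protocol 4.5). At 5% vs 3.5% the pooled rate is (45 + 15.75)/1350 = 0.045, SE is 0.0120 and z is about 1.25.
- *A reader might infer that the time-to-therapy analysis in SAP 5.2.15 has the same defect.* That section does not restrict the analysis to children with a detected pathogen.
- *A reader might infer that switching to receipt removes the testing advantage.* It does not, as the last step of the working shows.

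**Conclusion.** The point holds as a contradiction within the plan with a predictable direction. SAP 5.2.14, followed literally, analyses detection under the name of therapy received, conflicts with protocol 4.6, SAP 2.2.2 and SAP 2.6.2 row 14, and leaves the registered receipt outcome without a specified comparison.

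The expected bias towards point-of-care testing rests on two things: equal true prevalence between arms, and discretionary testing that finds a smaller share of carriers than routine testing does. Its size cannot be fixed from the documents. Across s = 0.2 to 0.8 the expected RR runs from 5.0 to 1.25 without failures, and from 4.2 to 1.05 with 16% failures throughout. Significance ranges from likely to unlikely over that span.

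This is a secondary outcome. The primary outcome, its analysis and the sample size are unaffected.

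**What to change.** Rewrite SAP 5.2.14 as follows.

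- **Numerator:** children who actually received antimicrobial therapy directed against a detected pathogen on the list in SAP 2.2.2.
- **Denominator:** all randomised children in the arm.
- **Time window:** to be stated by the sponsor, since the documents give none for this outcome.
- **Detection:** report separately, as descriptive test yield and not as therapy.
- **Interpretation:** state that receipt still depends partly on testing intensity, because a child who is never tested cannot count.

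Two items need settling alongside. Protocol Appendix 1 has no entry for *Legionella*, although SAP 2.2.2 and 2.6.1 treat it as having targeted treatment; these must be reconciled. SAP 2.10 names antibiotic prescriptions among the data collected but not antivirals, so extraction of antiviral prescriptions should be confirmed, given that influenza is on the list.

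The cost is SAP wording and one recoded variable, plus antiviral data if they were not already extracted. SAP 2.10 describes the record source as covering nearly all prescription data, so those data should be retrievable.
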